## Abstract

**Introduction::**

With the development of social economy, transportation and various infrastructures have also developed, but it has objectively increased the number of patients with head injury. Although the current craniocerebral medicine technology continues to advance, long-term bed rest and other complications have led to an insignificant decrease in the mortality rate of coma patients. It is not uncommon for patients with disturbance of consciousness caused by head injury in major hospitals.

**Methods/design::**

This will be a retrospective, single-blind clinical observational study. We will select 50 cases that meet the subject's selection criteria. According to whether they received acupuncture treatment or not, they will be randomly divided into 2 groups, namely treatment group and control group. The control group will be given conventional Western medicine treatment, and the treatment group will be given acupuncture method of removing-stasis and resuscitating treatment on the basis of the control group.

**Discussion::**

Our purpose is to observe the role of acupuncture method of removing-stasis and resuscitating in promoting the recovery of patients with severe head injury. We aim to provide more evidence-based medical evidence for acupuncture treatment of this disease.

**Trial registration::**

ClinicalTrials.gov, ChiCTR2000034732, Registered on 19 July 2020

## Introduction

1

Craniocerebral injury is damage to the brain tissue caused by violence directly or indirectly acting on the head. According to the Glasgow Coma Scale (GCS) method, it is determined that a person who is in a coma for more than 6 hours or becomes unconscious again after injury is a severe head injury. Craniocerebral injury manifests as disturbance of consciousness, headache, nausea, vomiting, seizures, limb paralysis, sensory disturbance, aphasia, and hemianopia. Skull base fractures can cause cerebrospinal fluid otorrhea; brainstem injury can cause disturbances in consciousness and breathing and circulation. In severe cases, brain herniation can endanger life. Among them, the change of consciousness after head injury is 1 of the most common symptoms of neurosurgery patients with head injury. Direct or indirect violence acting on the head and causing brain tissue damage is the main reason for craniocerebral injury and consciousness disturbance. Wang Yuhu^[1]^ discussed the causes of the onset of coma patients and believed that various lesions inside and outside the brain and the ascending activation system of the brainstem reticular structure can lead to disturbance of consciousness. With the continuous improvement of medical technology, the mortality rate of head trauma has decreased, but the mortality rate of severe head injury is still between 30% and 50%.^[2]^ Although the current craniocerebral medicine technology continues to advance, long-term bed rest and other complications have led to an insignificant decrease in the mortality rate of coma patients. It is not uncommon for patients with disturbance of consciousness caused by head injury in major hospitals. Every year, about 2 million people in China are in a coma due to head injury, and about 200,000 of them are in a persistent vegetative state. Unconsciousness within a week of trauma can easily lead to complications and comorbidities and become an important cause of death. Therefore, early awakening and reducing complications and complications are the key to reducing mortality. A large number of patients with impaired consciousness only rely on drugs to promote awakening with little effect, and long-term large amounts of drugs are likely to bring many toxic side effects to patients. In addition, the continuous coma adds a huge psychological and economic burden to the family members of the patient, so the recovery of the disease is particularly urgent. Traditional Chinese Medicine (TCM) believes that blood stasis to block the brain collaterals is the basic pathogenesis of head injury. The treatment should be based on removing blood stasis and resuscitation. As an important part of TCM, acupuncture therapy is widely used in the treatment of this disease. There are many traditional acupuncture treatment methods, mainly including “Xing Nao Kai Qiao” acupuncture, electroacupuncture, scalp acupuncture and ear acupuncture. Among them, the “*Xing Nao Kai Qiao*” acupuncture method established by Shi Xuemin^[3]^ has a definite effect on the pathological factor of stroke with congestion. To further explore the effect of acupuncture method of removing-stasis and resuscitating on the consciousness of patients with severe traumatic brain injury, we designed this experiment. Our purpose is to observe the role of the method of removing-stasis and resuscitating in promoting the recovery of patients with severe head injury. The specific plan is reported as follows.

## Methods/design

2

### Study design and settings

2.1

This will be a retrospective, single-blind clinical observational study. We will select 50 cases that meet the subject's selection criteria. According to whether they received acupuncture treatment or not, they will be randomly divided into 2 groups, namely treatment group and control group. The control group was given conventional Western medicine treatment, and the treatment group was given acupuncture method of removing-stasis and resuscitating treatment on the basis of the control group. After acupuncture, the needles are kept for half an hour, and acupuncture is performed every 10 minutes. Treatment is once a day, 5 times a week, with 2 days of rest, and 10 times is a course of treatment. Specialized researchers will record the unique clinical manifestations of the 2 groups of patients before and after treatment, coma GCS scores before and after treatment, recovery time, recovery rate, clinical efficacy and cure rate. We used statistical software SPSS25.0 to process the obtained data, and evaluated the clinical efficacy of the 2 groups based on the calculated results. (Fig. 1)

**Figure 1 F1:**
[figure not shown]
SPIRIT figure for the schedule of enrollment, interventions, and assessments. GCS = Glasgow coma scale, TCM = traditional Chinese medicine.

### Participants and recruitment

2.2

#### Participants

2.2.1

The case of this study will come from the Department of Neurosurgery of Wang Jing Hospital of China Academy of Chinese Medical Sciences, and the hospitalized patients who were diagnosed with craniocerebral injury and coma were diagnosed by Western medicine.

#### Inclusion criteria

2.2.2

(1)Have a history of head trauma, and be diagnosed by head imaging examination;(2)Age < 65 years old;(3)In a coma 6 h after injury, GCS score <8;(4)Those who have voluntarily signed the informed consent form;

#### Exclusion criteria

2.2.3

(1)Pregnant women, formerly mentally ill patients and senile dementia;(2)People with impaired consciousness caused by the primary disease;(3)During observation and treatment, the patient has severe vital signs disorder, irreversible brain stem damage, respiratory and circulatory failure, and serious complications such as high fever and infection;(4)Patients with tumor and other organ failure;

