#### Rejection, fall-off and suspension standards

2.2.4

(1)During the course of treatment and observation, the patient had other serious complications such as re-bleeding within a day and repeated intracranial hematoma removal;(2)During the treatment process, the family members of the patient did not cooperate, voluntarily gave up the treatment, or quit the treatment voluntarily because of other circumstances;(3)The cause of the coma cannot be determined, or the efficacy cannot be determined due to incomplete observation data;

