**Table 1 T1:**
[figure not shown]
Glasgow coma scale.

Efficacy criteria. This study will use the Glasgow Outcome Scale method for the final efficacy assessment. In this study, the results will be assessed after 3 months of treatment. Grade V (good): The patient is recovering well, can live a normal life, and has mild neurological disorders; Grade IV (moderate disability): Moderately disabled, but able to take care of themselves; Grade III: Severely disabled, clear consciousness, unable to live Self-care; Level II: Plant survival; Level I: Death. Total effective rate = (good + moderate disability)/total number of cases × 100%. Glasgow Outcome Scale Grading Scale^[6]^ (Table 2).

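### Exclusion and rejection rules triggered during treatment can remove patients whose poor outcomes the 3-month efficacy scale is meant to count, leaving the efficacy comparison open to bias

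*Protocol article*

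**What the plan says.** Three parts of the protocol article bear on this point.

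- **Section 2.2.3, Exclusion criteria, item (3).** The trigger is timed to the study period: "During observation and treatment, the patient has severe vital signs disorder, irreversible brain stem damage, respiratory and circulatory failure". The same item also names fever and infection as examples of complications that lead to exclusion.
- **Section 2.2.4, Rejection, fall-off and suspension standards.** Item (1), again timed to the study period, covers "other serious complications such as re-bleeding within a day and repeated intracranial hematoma removal". Item (2) covers families who do not cooperate and patients who "voluntarily gave up the treatment, or quit the treatment voluntarily because of other circumstances". Item (3) includes cases where "the efficacy cannot be determined due to incomplete observation data".
- **Section 2.6, efficacy criteria (text after Table 1).** Efficacy is graded on the GOS after 3 months of treatment. Grades III and II are severe disability and vegetative survival. The scale ends with the worst grade and the endpoint formula: "Level I: Death. Total effective rate = (good + moderate disability)/total number of cases × 100"%. The text does not say whether an excluded or rejected patient belongs in the denominator.

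Section 2.8 names the tests to be used but does not return removed patients to the analysis. As background, the Introduction states that "the mortality rate of severe head injury is still between 30% and 50"%.

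**The concern.** An exclusion criterion should describe the patient before allocation. Item (3) cannot work that way, because its wording ties it to what happens while the patient is observed and treated. In severe head injury, respiratory and circulatory failure, brainstem damage, re-bleeding and infection are plausible routes to the lower GOS grades. The same patient can therefore be both a case to remove and a case to score as unfavourable.

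Two things are at stake. First, each arm's effective rate is inflated whenever patients with unfavourable outcomes leave the denominator. Second, if the arms lose such patients at different rates, the groups compared are no longer those formed at allocation, and a difference can appear or be masked without any treatment effect. Unequal loss is possible: section 2.3 says participants and the assessor will know the allocation, and some reasons, such as a family giving up treatment or data judged insufficient, leave room for judgement.

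**Working it through.** The protocol states no sample size or power calculation (section 2.4 says none is done), so there is no figure of its own to reproduce. The check has two parts.

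**1. The passages side by side**

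| Event during the study | Sections 2.2.3 and 2.2.4 | Section 2.6 |
|---|---|---|
| Respiratory and circulatory failure, brainstem damage | Excluded | If fatal, Grade I; otherwise graded at 3 months |
| Re-bleeding, repeated surgery for haematoma | Rejected | Graded at 3 months |
| Treatment given up | Rejected | Graded at 3 months if followed |
| Incomplete data | Rejected | No rule |

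The two columns cannot both govern the same patient.

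**2. Possible size**

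Inputs from the document: 50 cases (section 2.1); background mortality 30% to 50% (Introduction); significance level 0.05 and chi-square test for counts (section 2.8).

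Assumptions, not in the document: 25 per arm, a true favourable rate of p = 0.30 in both arms, the removal shares below, and all removed patients unfavourable.

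*Deaths, if the background mortality applied here:* 50 × 0.30 = 15 and 50 × 0.50 = 25.

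*Inflation within one arm.* With a share r of the arm removed, the observed rate is p/(1 − r). For r = 0.20: 0.30/0.80 = 37.5%. For true rates of 20% and 40%, the same removal gives 0.20/0.80 = 25% and 0.40/0.80 = 50%.

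*Difference between arms under no true effect.* With a share q of the unfavourable patients removed, the observed rate is p/(1 − (1 − p)q).

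- q = 0.10: 0.30/(1 − 0.07) = 0.30/0.93 = 32.3%
- q = 0.40: 0.30/(1 − 0.28) = 0.30/0.72 = 41.7%
- q = 0.50: 0.30/(1 − 0.35) = 0.30/0.65 = 46.2%

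So 40% versus 10% gives 41.7 − 32.3 = 9.4 points, and 50% versus 10% gives 46.2 − 32.3 = 13.9 points.

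*Type I error.* Simulated with the uncorrected Pearson chi-square test at 0.05:

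| Removal pattern | False difference | Type I error |
|---|---|---|
| None (all randomised patients kept) | 0 | about 5% |
| 20% of each arm, all unfavourable | 0 (37.5% in both) | about 5% |
| 40% vs 10% of the unfavourable | about 9 points | about 10% |
| 50% vs 10% of the unfavourable | about 14 points | about 15% |

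Swapping the arms reverses the sign of the difference and leaves the error rate unchanged. The document does not indicate which arm would lose more.

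**The case against.** The strongest reply is that the article never says outright that a removed patient leaves the analysis. The heading of section 2.2.4 mixes rejection, drop-out and suspension; the denominator in section 2.6 could mean everyone enrolled; and analysis sets and missing-data rules are commonly left to a fuller document. This stands in part: removal from the analysis is inferred from the headings, and the withdrawal and incomplete-data items alone would be weak grounds. It does not dispose of the point. The deterioration rules are stated in this article, they conflict with its own outcome scale, and nothing in it puts the removed patients back. Nor can a later analysis plan recover 3-month outcomes that were never collected.

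Several stronger readings are tempting, and the text does not support them:

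- **That most deaths would be removed.** No frequency is given for the listed events, or for the share of deaths they precede. Grades II and III are not removal triggers in themselves, so a patient who stays in coma without a listed complication is scored.
- **That every removal follows allocation.** Section 2.3 places randomisation after baseline data collection, and section 2.5.1 starts acupuncture once the patient is stable. Some of the events may come first. Design statements elsewhere in the article (retrospective, grouped by whether acupuncture was received) further cloud when allocation occurs.
- **That unblinded staff decide the removals.** Section 2.3 describes the assessor as unblinded but does not say who applies these rules, and the sentence concerned describes an intervention that is not part of this trial.
- **That the comparison is certainly biased.** With equal removal the type I error stays near 5%.
- **That harms would vanish.** Leaving the efficacy analysis is not the same as going unreported, and section 2.4 names safety as a focus.
- **That 15 to 25 deaths should be expected.** The mortality figure is for severe head injury in general. This trial takes patients under 65 and waits for stability before needling.

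**Conclusion.** The point holds as a conflict between stated rules. Sections 2.2.3 and 2.2.4 allow removal on deterioration, complications, withdrawal or missing data that arise during the study. Section 2.6 grades the outcomes to which such events may lead, over a denominator it does not define. Two consequences differ in certainty. Inflation of an arm's effective rate follows whenever the removed patients are predominantly unfavourable (30% read as 37.5% at 20% removal). Distortion of the comparison needs unequal removal, may run in either direction, and has a size that cannot be derived from the document. The 9 to 14 points and the 10% to 15% type I error illustrate assumed removal shares and are not predictions. Because the efficacy result depends on who is counted, this should be settled before recruitment.

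**What to change.** 1. Limit exclusion criterion (3) to the patient's status before randomisation.
2. Reconcile sections 2.2.3, 2.2.4 and 2.6 so that meeting a criterion in 2.2.4 does not by itself remove a patient from the efficacy analysis. Leaving the analysis and stopping treatment should be separate matters; any rule on stopping treatment is for the investigators.
3. Seek the 3-month GOS for every randomised patient unless consent to follow-up is withdrawn.
4. Define the denominator of the total effective rate as all randomised patients in their allocated arm, with death scored as Grade I.
5. Add a sensitivity analysis for missing GOS, and present any per-protocol analysis as secondary only.
6. Tabulate the events listed in 2.2.3(3) and 2.2.4 by arm as safety data.

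The cost is protocol wording, 3-month follow-up of patients who have stopped treatment, and lower stated effective rates. Under the assumptions above, keeping all randomised patients brings the false difference to zero and the type I error to about 5%, provided their 3-month outcomes are obtained.

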#### Rejection, fall-off and suspension standards

2.2.4

(1)During the course of treatment and observation, the patient had other serious complications such as re-bleeding within a day and repeated intracranial hematoma removal;(2)During the treatment process, the family members of the patient did not cooperate, voluntarily gave up the treatment, or quit the treatment voluntarily because of other circumstances;(3)The cause of the coma cannot be determined, or the efficacy cannot be determined due to incomplete observation data;

### Sample size determination

2.4

Since this is a pilot study, we will not perform calculations to determine the sample size for this study. Instead, the focus will be on the feasibility and safety of the research. We plan to recruit at least 60 participants with a retention rate of 80%.

### Intervention method

2.5

#### Basic treatment protocol

2.5.1

We will require patients to stay in bed absolutely and give them oxygen to keep their airways open. Patients with severe breathing disorders may undergo tracheotomy. Patients with indications for brain surgery will be treated with surgery. Our goal is to prevent and treat cerebral edema, gastrointestinal bleeding and other complications. In addition, we will also carry out routine neurosurgical treatment and nursing care for patients, such as infection control, supplementation of energy polarizing fluid and nutritional supply. When the patient's vital signs and condition are stable, they will be given acupuncture to promote awakening and assist in treatment.

#### Control group

2.5.2

The control group will be given conventional comprehensive treatment of western medicine, dehydration, hemostasis, and nourishment of brain cells (intravenous infusion of monosialic acid ganglioglyceride 80 mg, 1 time/d, after 2 weeks of continuous use, change to 40 mg, 1 time/d, then use 4 to 6 weeks; intravenous infusion of calf serum 1.6 g, once a day, for 2 weeks), surgical treatment will be performed in time when there are surgical indications. At the same time, we will pay close attention to changes in blood sugar, electrolytes and liver and kidney function to prevent and treat complications such as gastrointestinal bleeding.

#### Treatment group

2.5.3

The treatment group will be given acupuncture treatment on the basis of the control group. We will select the following acupoints as the main acupuncture sites: Baihui, Sishenchong, Neiguan, Sanyinjiao, Xuehai, Fengchi, Quchi, Shuigou. Baihui is located at the intersection of the middle line of the head and the tip of the ears. It is closely connected with the brain and is the key point for regulating brain function. Baihui is the place where all meridians converge. Being able to reach the yin and yang veins and connect the meridians throughout the body plays an important role in regulating the balance of yin and yang in the body. Sishenchong is located 1 inch apart from the front, back, left, and right sides of Baihui on the top of the head, with a total of 4 acupuncture points. There are branches of the greater occipital nerve, ear cervical nerve and supraorbital nerve around this point. This acupuncture point mainly treats madness, epilepsy, stroke, hemiplegia, forgetfulness, insomnia, headache, dizziness, cerebral hypoplasia, hydrocephalus, head pain, and so on. Pierce 0.5–0.8 inches horizontally. The Neiguan is located 2 inches above the transverse crease of the forearm, between the palmar longus tendon and the flexor carpi radialis tendon. This point is commonly used in modern times to treat angina, myocarditis, arrhythmia, gastritis, hysteria, and so on. Pierce the skin 0.5 to 1 inch vertically. Sanyinjiao is an acupuncture point of the body. Sanyinjiao refers to the intersection of qi and blood in the 3 meridians with yin attributes on the feet. Xuehai is on the inner thigh, 2 inches above the medial end of the patellar base, and is located on the bulge of the medial head of the quadriceps when the knee is bent. Fengchi is located on the back of the neck, under the back of the skull, in the lacuna on the outer edge of the two large tendons, equivalent to the level of the earlobe. Fengchi is in the depression between the attachment between the sternocleidomastoid muscle and the upper end of the trapezius muscle. The deep layer is the splinter muscle; there are branches of occipital arteries and veins; and the minor occipital nerves are distributed. Quchi is located at the lateral end of the elbow transverse striae, at the midpoint of the line between Chize and the lateral epicondyle of the humerus when the elbow is bent. This acupuncture point has the functions of clearing away heat and removing the surface, dredging the channels and collaterals. Shuigou is on the face, at the intersection of the upper 1/3 and the middle 1/3 of the middle groove. The acupoints are distributed with the infraorbital nerve branch and the buccal branch of the facial nerve. This acupoint is mainly used for coma, syncope, heatstroke, madness, epilepsy and other diseases. Needle insertion method: puncture 0.3 to 0.5 inch diagonally upward.

Treatment time and duration. This study will use the method of moving the needle for half an hour. Acupuncture is performed once every ten minutes, once a day, 5 days a week, 10 times as a course of treatment, GCS score is recorded every 3 courses of observation, and recorded twice in a row.

### Outcome measures

2.6

(1)There are specific indications for awakening precursors.^[4]^ We will observe the patient's specific clinical manifestations (spraying reflex and limb restlessness) during acupuncture treatment as specific indications for awakening;(2)GCS scoring standard.^[5]^ We will perform GCS scoring on the two groups of patients before and after treatment on the 30th, 60th, and 90th day. GCS ≤ 8 points is defined as coma, GCS ≥ 9 points is defined as awakening (according to the specific clinical situation, most patients have a tracheotomy that affects the observation of the pronunciation response, so the patient's action is used as the observation scoring basis). (Table 1)

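### Awakening keeps the full-scale GCS cut-off of 9, although tracheotomy is said to affect the verbal item in most patients and the scored components are not stated

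*Protocol article*

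**What the plan says.** Item (2) of section 2.6 (Outcome measures) sets the threshold: "GCS ≤ 8 points is defined as coma, GCS ≥ 9 points is defined as awakening". A parenthesis in the same sentence gives a practical difficulty, that "most patients have a tracheotomy that affects the observation of the pronunciation response", and then the response to it: "so the patient's action is used as the observation scoring basis". The section names no components for the score in these patients, no value for the verbal item and no adapted cut-off. It also does not make clear whether the rule covers everyone or only patients with a tube.

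The score is to be taken "before and after treatment on the 30th, 60th, and 90th day". Section 2.1 lists the quantities to be recorded, among them "coma GCS scores before and after treatment, recovery time, recovery rate, clinical efficacy and cure rate". Neither recovery time nor recovery rate has a definition of its own. The Discussion repeats that most patients of this kind need a tracheotomy.

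Section 2.6 also specifies the Glasgow Outcome Scale at three months as the final measure of efficacy, with its own responder rate.

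**The concern.** A threshold of 9 belongs to a total built from eye, verbal and motor responses. Once the protocol says that one of the three is affected in most patients and moves the scoring to another basis, the threshold has to move with it or be justified again. Here the basis changes and the threshold does not.

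At stake is whether the awakening outcome measures return of consciousness, which is the trial's question. Two assessors who read the parenthesis differently could class the same patient as awake and as in coma. Section 2.3 says that the person who assesses outcomes will know the allocation, so an open scoring rule would be applied without the protection of blinding. Section 2.2.2 sets the entry score without any adjustment for tracheotomy, so baseline and follow-up may also be scored on different bases.

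**Working it through.** The protocol derives no figure for this point, so there is none to reproduce. The check is to list every component combination and compare it with the cut-off.

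**Inputs**
- Cut-off: 8 or less is coma, 9 or more is awakening (section 2.6).
- Verbal response affected in most patients, no percentage given; action used as the scoring basis (section 2.6).
- Assumed: standard ranges eye (E) 1-4, verbal (V) 1-5, motor (M) 1-6, with M6 meaning that the patient obeys commands. Table 1, which carries the scale, is not shown.

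**Three ways to form the score without a usable verbal item**
- Motor only: score = M, maximum 6.
- Eye plus motor: score = E + M, maximum 4 + 6 = 10.
- Verbal set to 1: score = E + 1 + M, maximum 4 + 1 + 6 = 11.

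There are 4 × 6 = 24 eye/motor pairs. The seven below are all the pairs that either obey commands or reach 9 under at least one of the three rules.

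| Pair | Obeys commands | Motor only | Eye + motor | Verbal = 1 |
|---|---|---|---|---|
| E1M6 | yes | 6, coma | 7, coma | 8, coma |
| E2M6 | yes | 6, coma | 8, coma | 9, awake |
| E3M6 | yes | 6, coma | 9, awake | 10, awake |
| E4M6 | yes | 6, coma | 10, awake | 11, awake |
| E3M5 | no | 5, coma | 8, coma | 9, awake |
| E4M4 | no | 4, coma | 8, coma | 9, awake |
| E4M5 | no | 5, coma | 9, awake | 10, awake |

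**Results**
- Motor only: no pair reaches 9.
- Eye plus motor: three pairs reach 9 (E3M6, E4M5, E4M6). One of them does not obey commands (E4M5), and two command-following pairs are called coma (E1M6, E2M6).
- Verbal set to 1: six pairs reach 9. Three of them do not obey commands (E3M5, E4M4, E4M5), and one command-following pair is called coma (E1M6).

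**Two further rules, as a sensitivity check**
- Motor score entered in the verbal slot, capped at 5 (score = E + min(M, 5) + M): ten non-obeying pairs reach 9. One is E1M4, since 1 + 4 + 4 = 9.
- Eye plus motor prorated to 15 (score = 1.5 × (E + M)): ten non-obeying pairs reach 9. One is E4M2, since 1.5 × 6 = 9.

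Under both of these rules every command-following pair reaches 9, so the error runs only towards calling patients awake. These are counts of score patterns, not of patients, and give no misclassification rate.

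**The case against.** The strongest defence is that the wording is loose but need not be wrong. It does not say that action is the only thing scored or that eye opening is dropped. It could mean that the response speech would have shown is judged from behaviour, which would keep three components and the cut-off. An adapted scale could stand in Table 1, which is not shown, or in a fuller protocol. A total of 9 does not guarantee command-following on the full scale either.

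Part of this stands. A reader might infer that awakening is impossible in tracheotomised patients whatever the treatment does, but that follows only if the motor item alone is scored, which the text does not establish. A reader might also conclude that the cut-off must be either out of reach or met by unresponsive patients. That does not follow: with eye plus motor, 9 can be reached, and all three pairs that reach it localise or obey.

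Three further inferences go beyond the documents:
- That a patient at E4 V1 M4 would be graded vegetative in section 2.6. The outcome grade reads only "Level II: Plant survival" and is not tied to GCS components.
- That the entry rule, "In a coma 6 h after injury, GCS score <8", contradicts the coma definition. An entry limit may be stricter than an outcome definition.
- That removing a tube makes the score jump. This holds only if the substitute rule applies to tracheotomised patients alone, which is left open.

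The defence does not remove the main point. The threshold and the change of scoring basis stand in one sentence and are not reconciled. Judging the verbal response from behaviour would still need a conversion rule, and none is stated.

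**Conclusion.** The point holds in a limited form. The protocol article combines an unadjusted GCS cut-off of 9 with a scoring basis that, by its own account, departs from the full scale in most patients. Each of the five scoring rules computed misclassifies some patients, but not in the same direction. Motor only can never show awakening. Eye plus motor calls two command-following patterns coma and one non-obeying pattern awake. Verbal set to 1 calls three non-obeying patterns awake and one command-following pattern coma. The other two rules only over-call awakening.

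The consequence is confined to the awakening outcome and, if they are based on it, to recovery rate and recovery time. That link is plausible, because no other definition of awakening is given, but it is not stated. The Glasgow Outcome Scale measure does not use the cut-off and is not affected.

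The conclusion rests on standard component ranges and on command-following as the marker of consciousness. The number of patients affected cannot be given, because the documents report neither the share with a tracheotomy as a figure nor the distribution of scores.

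**What to change.** Reconcile the cut-off with the scoring basis in section 2.6:

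1. Record the eye, verbal and motor components separately at each assessment, not just a total.
2. Mark the verbal item as not testable in tracheotomised patients instead of entering a number.
3. Analyse the GCS course on eye plus motor in all patients, with or without a tube.
4. Use one awakening definition that does not depend on the verbal item, applied identically with and without a tube, at baseline and at days 30, 60 and 90. Obeying commands (motor score 6) is one workable example.
5. State whether recovery rate and recovery time use this definition.

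The cost is a few lines of definition and separate component fields on the case report form. The downside of the motor-6 example is that some conscious patients with aphasia would be classed as not awake, and the protocol should say so. The change should come before data collection, because a total stored without its components cannot be re-scored later.
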